**Research protocol**

**Project summary**

Fear of childbirth (FOC) is a risk factor for maternal and child adverse outcomes and needs to be addressed during pregnancy. In this study, we aim to determine the effect of an mHealth application based on continuous support and education on FOC, self-efficacy, and birth mode in primiparous women. This study will be a single-center, Randomized Controlled Trial (RCT). It will conduct on seventy primiparous pregnant women with FOC attending a university-dependent governmental hospital in Tehran, Iran. Women who meet the inclusion criteria will randomly assign to two parallel intervention and control groups. Study participants in the intervention group will receive an mHealth application named Tele-midwifery, an interactive application based on multipurpose approaches, such as education and consultation, emphasizing continuous care for eight weeks. Women in the control group will receive routine prenatal care. FOC and self-efficacy will be measured via Wijma Delivery Expectancy/Experience (W-DEQ) questionnaire and Childbirth Self-efficacy Inventory (CBSEI), respectively. Data will be collected at the beginning of the study, 36 weeks of pregnancy, and after childbirth. Data will be analyzed by SPSS-25 using Chi-square, Fisher’s exact test, independent t-tests, and repeated-measures analysis of variance. We hypnotize that the intervention in this study will improve the FOC score, increase self-efficacy, and lower the number of C-sections.

**Rationale and background information**

Fear of Childbirth (FOC) affects almost 14 percent of women severely and there is an increasing trend in the number of women experiencing FOC during their life course (1). Women suffering from FOC usually experience nightmares, physical complaints, and a lack of focus on work or social life (2). FOC is related to increased emergency and elective C-sections (CS) (3). Moreover, women with FOC experience more complications such as preterm birth, prolonged labor, dystocia, postpartum depression, post-traumatic stress disorder, and less mother-child bonding (4-8). FOC is strongly associated with a lack of childbirth self-efficacy, especially in nulliparous women; therefore, the effort to increase self-efficacy is a practical part of a successful strategy to improve FOC (9). Some interventions have been shown to be effective; however, there is no consensus regarding the best treatment for alleviating women's fears. Additionally, most of these interventions are in-person and are related to high costs and difficulty in implementation (7). Due to these challenges, digital methods such as mHealth applications have gained attention in various fields to improve women's health. Receiving pregnancy-related services including information and consultation by digital technologies such as mHealth applications are shown to be acceptable by pregnant women, leading to positive pregnancy and childbirth experiences (10). Receiving health care through mHealth, make patients more responsible for obtaining information and learning; thus, more in-depth knowledge and awareness would acquire, which are factors related to reducing FOC and increasing self-efficacy (11). The application of mHealth interventions to improve the FOC and its related factors including self-efficacy and birth mode have received less attention among Iranian pregnant women. This method may reduce the FOC, increase women's self-efficacy and the number of CS. Therefore, in this study, an mHealth application will consider a possible strategy for treating women with FOC.

**Study goals and objectives**

1) Women receiving the Tele-midwifery intervention will report lower levels of FOC compared to the control group.

2) Women receiving the Tele-midwifery intervention will have a higher self-efficacy score compared to the control group.

3) Women receiving the Tele-midwifery intervention will have a lower number of CS compared to the control group.

**Study design**

This study will be is an RCT with two groups of control and intervention, and will be conduct on seventy primiparous women who will attend the prenatal clinic of one of the public university hospitals in Tehran, Iran (Baharlou), to receive prenatal care from February to April 2020.

**Inclusion criteria**:

Inclusion criteria in this study will be: being primiparous, having FOC (confirmed by the score of 38 and above on the Wijma Delivery Expectancy/Experience Questionnaire (W-DEQ)), being aged between 18 to 40 years, being pregnant with a singleton fetus, being in 26-29 weeks of pregnancy, having access to a smart device such as smartphone, or a tablet (women or their spouses), as well as the ability to work with them, having access to the internet, not having chronic diseases and CS indications before or during pregnancy.

**Exclusion criteria:**

The exclusion criteria will be, emergency pregnancy conditions that require further medical interventions (e.g., placental abruption, fetus abnormalities, preeclampsia).

### Methodology

**Outcomes**

The primary outcome of this study will be change in FOC score, and the secondary outcomes will be change in childbirth self-efficacy score, and birth mode.

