**Measures**

The FOC will be measured using W-DEQ versions A and B. W-DEQ version A evaluates women's prenatal expectances before childbirth, and W-DEQ version B evaluates experiences with recent childbirth. Each version contains 33 items with a 6-point Likert scale ranging from 0 (extremely) to 5 (not at all), and scores range from 0 to 165, with higher scores indicating higher fear of childbirth (12). According to this questionnaire, a score less than or equal to 37 represent mild fear, a score of 38-65 represents a moderate level, 66-84 represents high level of fear, and a score more than 85 shows a severe level of fear. The reliability of the W-DEQ version A and B questionnaire for nulliparous women was confirmed with Cronbach's alpha of 0.89 and 0.92, respectively (12). The validity and reliability of the Persian version of this questionnaire for Iranian women have been confirmed (13).

The Childbirth Self-Efficacy Inventory (CBSEI) is a self-report instrument that measures outcome expectancies (OE) and efficacy expectancies (EE) for coping with an approaching childbirth experience. This questionnaire has two parts and 62 items that scored on a ten-point Likert scale (1= not at all; 10= completely sure), with a higher score indicating greater childbirth self-efficacy. The reliability of the questionnaire has been confirmed with Cronbach's alpha 0.86-0.95 (14). The validity and reliability of the Persian version of this questionnaire were assessed by Khorsandi et al. (2008). In their study, high internal consistency with Cronbach's alpha coefficient of 0.84 to 0.91 was reported for the CBSEI (15).

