**Procedures**

A convenient sampling approach will be used, and a consecutive sample of pregnant women attending the selected prenatal clinic (located in Baharlou hospital) for receiving their routine prenatal care will be evaluated by their medical records for inclusion and exclusion criteria, by a colleague not involving in the study. Afterward, the objectives and goal of the study will be explained to eligible pregnant women, and after filing the consent form, they will be asked to complete the W-DEQ version A. women with a score of 38 and above (moderate and high FOC score) will be enrolled the study.

A randomized allocation into two groups of intervention and control with a 1: 1 ratio will be taken place during the routine prenatal visit in the hospital by a colleague who will be not involved in the study and computerized generated random sequences. In both intervention and control groups, the Tele-midwifery application will be installed on their smartphones during their prenatal visit. This application will only allow access to the questionnaires in the post-test, and follow-up stages for the participants in the control group. To prevent information contamination to the control group, after installing the application and before activating their account, women must select their group type as A or B. In addition, we will ask women in both groups to avoid sharing the contents of the application with each other for the duration of the trial. The Tele-midwifery application have two main stages for answering the questions. After filling the baseline questionnaire in the initial registration, including demographic, W-DEQ, and CBSE questionnaires, each group’s participants will complete the W-DEQ and CBSE questionnaires again at 34-36 weeks (after eight weeks of receiving the intervention). Participants will be also asked to inform the researcher by sending a message after hospitalization for their birth, whether in the Tele-midwifery application or by contacting the researcher directly by her phone number. Afterward, the W-DEQ version B questionnaire will appear in the application within the first two hours after birth, and the birth mode will be recorded. The investigators, care providers, data collectors, and statisticians will be masked from the allocation.

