### Data management and statistical analysis

The data will be analyzed using SPSS software version 25, and p-value > 0.05 will consider a statistically significant level. First, the Kolmogorov‐Smirnov test will use to examine the normal distribution of data. After determining the normal distribution of data, to compare statistical differences of demographic data in two groups, an independent t-test, Chi-square test, and Fisher's exact test will be used. Also, for analyzing outcome variables, **r**epeated-measures analysis of variance (ANOVA) with a pairwise comparison of groups with Bonferroni correction, independent t-test, and Chi-square will determine the differences between the groups. **Sample size**

The sample size was calculated based on the results of Gözde Birsbir et al. (2016) study (18). A sample size of 70 pregnant women (35 in each group) was estimated. A two-sided t-test of difference between means with the power of 90%, the type one error equal to 0.05, mean difference of 21 between groups, and standard deviation of 7.2 was consider calculating the sample size. We accounted 20% attrition rate in estimating the sample size.

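### The primary outcome, change in fear-of-childbirth score, names neither a W-DEQ version nor a time point, and its post-birth measurement has no like-for-like baseline

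*Protocol*

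**What the plan says.** The Outcomes section gives a single primary outcome: "The primary outcome of this study will be change in FOC score". The first hypothesis, under Study goals and objectives, expects less fear in the intervention group and also names no version or time.

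Under Measures, both versions count as the outcome: "The FOC will be measured using W-DEQ versions A and B". The same section separates what they measure: "W-DEQ version A evaluates women's prenatal expectances before childbirth, and W-DEQ version B evaluates experiences with recent childbirth".

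Procedures sets three occasions:

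- **Enrolment:** "they will be asked to complete the W-DEQ version A".
- **Second assessment:** participants "complete the W-DEQ and CBSE questionnaires again at 34-36 weeks (after eight weeks of receiving the intervention"). The version is not named, but women are still pregnant, so by the Measures definition it must be A.
- **After delivery:** "the W-DEQ version B questionnaire will appear in the application within the first two hours after birth".

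The Project summary also lists three collection times. The analysis section says that repeated-measures "analysis of variance (ANOVA) with a pairwise comparison of groups with Bonferroni correction, independent t-test, and Chi-square will determine the differences between the groups". No test, contrast or occasion is designated primary. The sample size rests on one two-sided t-test at 0.05 that is not tied to a version or a time.

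**The concern.** Two problems follow from the one undefined phrase.

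The first is meaning. Version B cannot be completed before birth, so it has no baseline of its own. Any post-birth change has to subtract an expectation score from an experience score. The common 33 items and 0-165 range do not turn these into the same quantity, because the Protocol itself says they measure different things. Version B also describes the birth, whose mode is a separate secondary outcome, so a difference on B need not reflect less antenatal fear.

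The second is choice. With two follow-up occasions and none named, a result at either could be reported as the primary finding. The single comparison for which 5% error and 90% power were specified is never identified.

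**Working it through.** **1. The occasions side by side**

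| Occasion | Version | Construct |
|---|---|---|
| Baseline (26-29 weeks) | A | expectation |
| 34-36 weeks | A (by definition) | expectation |
| Within two hours after birth | B | experience |

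Write A0 for baseline, A1 for 34-36 weeks and B for after birth. Then A1 − A0 is change in one construct. The other available difference splits as

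B − A0 = (A1 − A0) + (B − A1),

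where the second bracket is experience minus expectation. It is not change over time in fear of the coming birth.

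Randomisation balances A0 on average, so the expected group difference in B − A0 equals the expected group difference in B. The randomised comparison of B is therefore sound in itself. What fails is calling it change, or treating B as a third level of the same repeated measure.

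**2. Inputs for the error rate**

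- Type I error 0.05, two-sided (Sample size).
- 35 per group with 20% attrition (Sample size): 35 × (1 − 0.20) = 28 analysed per group.
- Correlation between occasions: not given. Assumed 0.3 to 0.7, with 0 as a reference.

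The Protocol gives no overall error rate other than 5%, which is correct for one pre-named test. Its sample size does not identify the intended comparison, and it does not reproduce from its own inputs: 2 × (7.2 × (1.960 + 1.282) / 21)² = 2.47, so 3 per group before attrition. That is a separate matter, and nothing below depends on it.

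**3. Either follow-up test counts as success**

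If the two tests were independent: 1 − (1 − 0.05)² = 0.0975.

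Simulation with no treatment effect, 28 per group, 20,000 trials per setting, equal correlation between occasions:

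| Correlation | Either of two follow-up t-tests at 0.05 | Either of two change-from-baseline t-tests at 0.05 | Either follow-up t-test, each at 0.025 |
|---|---|---|---|
| 0 | 9.9% | 9.3% | 5.1% |
| 0.3 | 9.7% | 9.3% | 4.9% |
| 0.5 | 9.2% | 9.1% | 4.8% |
| 0.7 | 8.2% | 9.0% | 4.2% |

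A second simulation (10,000 trials per setting), with the A-B correlation set to 0.7 times the A-A correlation, gave 9.0-9.9% for the two follow-up t-tests. The range is thus about 8-10%.

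**4. Bounds under other readings**

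- Worst case, where the ANOVA group or group-by-time term may also count as success: 12.9-14.8% in the first simulation, so about 13-15%.
- Gated reading, where the group-by-time term and a follow-up t-test must both be significant: about 2%.

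**The case against.** The best defence is that the analysis section can be read benignly: an omnibus ANOVA, then corrected comparisons, with the t-test reserved for version B. Under that gated reading the error rate is about 2%. Test hierarchy is also commonly left to a statistical analysis plan, which is not at hand. Both points stand as far as they go. They do not excuse the missing version and time point, which belong in the Protocol's definition of its primary outcome.

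Several stronger readings are tempting but unsupported:

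- **That A, A and B certainly enter one ANOVA.** Three collection times and a single fear outcome suggest it, but no sentence says which scores enter the model.
- **That the planned error rate is 13-15%.** This needs any one of four tests to count as success, which the Protocol never says.
- **That the Bonferroni correction does nothing.** Taken literally, two groups form one pair. But the phrase sits beside a repeated-measures analysis and may mean group comparisons across occasions. Applied to the two follow-ups, it would hold the error near 5%. The wording is ambiguous.
- **That the ANOVA would lose most of its power if the application reduced only antenatal fear.** The group main effect is diluted. The group-by-time term, which is the one that matters for change, kept roughly 58-85% power for an assumed effect of 0.7 SD at the second version A only, against about 73% for a t-test at that occasion.
- **That version B is co-primary, or that comparing it is invalid.** No section gives it that status, and the randomised comparison stands.

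**Conclusion.** The point holds. The stated primary endpoint is ambiguous in version and time. One of its possible readings, change to after birth, mixes two constructs that the Protocol itself distinguishes. This part rests on the text alone and needs no assumption.

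The numerical part is conditional: about 8-10% type I error against 5%, if either unadjusted follow-up test is accepted as success, with 28 analysed per group and assumed correlations of 0.3-0.7. The figure of 13-15% is a worst case only. The flaw sits in the primary endpoint, so it should be settled before any outcome is analysed.

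**What to change.** - Define the primary endpoint as the W-DEQ version A score at the 34-36 week assessment. Name the version in Procedures, and state the time in the same way in the Project summary, which says 36 weeks.
- Specify one between-group test at two-sided 0.05, preferably adjusted for baseline version A. With equal SDs and correlation r, the outcome variance relative to the unadjusted score is 2(1 − r) for a change score and 1 − r² after adjustment. That is 1.40 against 0.91 at r = 0.3, and 0.60 against 0.51 at r = 0.7.
- Make version B a separate secondary outcome, compared between groups after birth. Do not use it as a change score or as a level of the repeated-measures model.
- Label the remaining fear analyses as supportive, and state which comparisons the Bonferroni correction covers.

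The cost is wording in the outcome, procedures and analysis sections, with no new data or visits. The real concession is that a difference seen only on version B after birth could no longer support the primary claim.

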**Measures**

The FOC will be measured using W-DEQ versions A and B. W-DEQ version A evaluates women's prenatal expectances before childbirth, and W-DEQ version B evaluates experiences with recent childbirth. Each version contains 33 items with a 6-point Likert scale ranging from 0 (extremely) to 5 (not at all), and scores range from 0 to 165, with higher scores indicating higher fear of childbirth (12). According to this questionnaire, a score less than or equal to 37 represent mild fear, a score of 38-65 represents a moderate level, 66-84 represents high level of fear, and a score more than 85 shows a severe level of fear. The reliability of the W-DEQ version A and B questionnaire for nulliparous women was confirmed with Cronbach's alpha of 0.89 and 0.92, respectively (12). The validity and reliability of the Persian version of this questionnaire for Iranian women have been confirmed (13).

The Childbirth Self-Efficacy Inventory (CBSEI) is a self-report instrument that measures outcome expectancies (OE) and efficacy expectancies (EE) for coping with an approaching childbirth experience. This questionnaire has two parts and 62 items that scored on a ten-point Likert scale (1= not at all; 10= completely sure), with a higher score indicating greater childbirth self-efficacy. The reliability of the questionnaire has been confirmed with Cronbach's alpha 0.86-0.95 (14). The validity and reliability of the Persian version of this questionnaire were assessed by Khorsandi et al. (2008). In their study, high internal consistency with Cronbach's alpha coefficient of 0.84 to 0.91 was reported for the CBSEI (15).

**Procedures**

A convenient sampling approach will be used, and a consecutive sample of pregnant women attending the selected prenatal clinic (located in Baharlou hospital) for receiving their routine prenatal care will be evaluated by their medical records for inclusion and exclusion criteria, by a colleague not involving in the study. Afterward, the objectives and goal of the study will be explained to eligible pregnant women, and after filing the consent form, they will be asked to complete the W-DEQ version A. women with a score of 38 and above (moderate and high FOC score) will be enrolled the study.

A randomized allocation into two groups of intervention and control with a 1: 1 ratio will be taken place during the routine prenatal visit in the hospital by a colleague who will be not involved in the study and computerized generated random sequences. In both intervention and control groups, the Tele-midwifery application will be installed on their smartphones during their prenatal visit. This application will only allow access to the questionnaires in the post-test, and follow-up stages for the participants in the control group. To prevent information contamination to the control group, after installing the application and before activating their account, women must select their group type as A or B. In addition, we will ask women in both groups to avoid sharing the contents of the application with each other for the duration of the trial. The Tele-midwifery application have two main stages for answering the questions. After filling the baseline questionnaire in the initial registration, including demographic, W-DEQ, and CBSE questionnaires, each group’s participants will complete the W-DEQ and CBSE questionnaires again at 34-36 weeks (after eight weeks of receiving the intervention). Participants will be also asked to inform the researcher by sending a message after hospitalization for their birth, whether in the Tele-midwifery application or by contacting the researcher directly by her phone number. Afterward, the W-DEQ version B questionnaire will appear in the application within the first two hours after birth, and the birth mode will be recorded. The investigators, care providers, data collectors, and statisticians will be masked from the allocation.

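### App access to the intervention rests on a group letter the woman enters herself, with no stated check, and the CBSEI baseline as narrated follows allocation

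*Protocol*

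**What the plan says.** All the steps are in the Procedures section of the Protocol, in this order.

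1. Consent, then screening: "after filing the consent form, they will be asked to complete the W-DEQ version A". A score of 38 or more is needed to enrol.
2. Allocation: "A randomized allocation into two groups of intervention and control with a 1: 1 ratio will be taken place during the routine prenatal visit". A colleague outside the study does this from a computer-generated sequence.
3. The app is installed on phones in both groups. For controls: "This application will only allow access to the questionnaires in the post-test, and follow-up stages for the participants in the control group".
4. As the measure against contamination: "after installing the application and before activating their account, women must select their group type as A or B".
5. The later questionnaires are introduced with: "After filling the baseline questionnaire in the initial registration, including demographic, W-DEQ, and CBSE questionnaires".
6. Masking: "The investigators, care providers, data collectors, and statisticians will be masked from the allocation". Participants are not in this list.

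Under Outcomes: "The primary outcome of this study will be change in FOC score". Change in self-efficacy is a secondary outcome. Both therefore depend on a baseline score.

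**The concern.** Two weaknesses follow from the procedure as written.

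The first is control of access. One app serves both arms, and the letter a woman enters decides whether the education, the forum and contact with the research team open. The step meant to prevent contamination is thus itself a possible route for it, by mistake or on purpose.

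The second is the timing of baseline. Self-reported fear and self-efficacy can shift once a woman knows what she has been offered. If the baseline is answered at that point, a difference between arms caused by knowledge of allocation enters the change score and cannot be separated from the treatment effect. For the CBSEI no earlier measurement is described. For the W-DEQ there appear to be two early scores, and the Protocol does not say which of them is the baseline.

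**Working it through.** **Access.** A random allocation exists before the letter is entered (steps 2 and 4 above). The letter is entered by the woman, before her account is activated. The Protocol does not say who activates the account, whether the letter is pre-filled, or whether it is compared with the list. So the assigned group is random, while the content received depends on an unverified entry.

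**Baseline.** Read in order, screening W-DEQ A precedes allocation, and the registration questionnaires are described after allocation, installation and the A/B step. That order is implied by the narrative, not stated.

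| Measure | Described before allocation | Described at registration |
|---|---|---|
| W-DEQ | yes (version A, screening) | yes |
| CBSEI | no | yes |
| Demographics | no | yes |

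The between-group difference in change is (follow-up difference) − (baseline difference). If knowledge of the group moves the baseline of one arm by x points, the estimate moves by x points. The documents give no basis for a value of x.

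**Wrong entries: effect.** Let a share q of each arm enter the wrong letter and receive the other arm's content throughout, with analysis as randomised. The difference Δ becomes Δ(1 − q) − Δq = Δ(1 − 2q). For Δ = 21 (Data management and statistical analysis, sample size):

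- q = 5%: 21 × 0.90 = 18.9
- q = 10%: 21 × 0.80 = 16.8
- q = 20%: 21 × 0.60 = 12.6

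**Wrong entries: power.** The sample-size text states: "A two-sided t-test of difference between means with the power of 90%, the type one error equal to 0.05", with a difference of 21, SD 7.2, 20% attrition and 35 per group. These inputs do not reproduce 35. The exact t-test needs 3.75, so 4 per arm, and 4 / 0.8 = 5 after attrition. That is a separate matter, but it means that any power figure depends on the effect size one uses. With 35 × 0.8 = 28 evaluable per arm, there are two bases:

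- (a) the stated inputs, 21 / 7.2 = 2.92 SD;
- (b) the effect for which 28 per arm gives exactly 90% power, 0.882 SD by the two-sided t-test. This is back-solved and stands nowhere in the Protocol.

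Mixing two kinds of exposure within an arm also raises the SD to √(SD² + q(1 − q)Δ²). Example for (b) at q = 10%: effect 0.882 × 0.8 = 0.706; SD √(1 + 0.09 × 0.882²) = 1.034; ratio 0.682; power 71%. Leaving out the added variance gives 74%.

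| q per arm | (a) power | (b) power |
|---|---|---|
| 0% | above 99% | 90% |
| 5% | above 99% | 82% |
| 10% | above 99% | 71% |
| 20% | about 99% | 45% |

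The shares q are assumptions. The Protocol gives no expected rate of wrong entries.

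**The case against.** **Women do not choose their arm.** Because a colleague randomises first, selecting A or B most naturally means entering the letter already assigned. This stands. A reader might infer that self-selection replaces randomisation or breaks it outright. The Protocol does not support that: nothing says that app records define the analysis groups, and an analysis by the allocation list remains a randomised comparison. The choice of analysis set may also sit in an analysis plan that is not shown.

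**A baseline W-DEQ before allocation exists.** This stands too. It would be wrong to infer that the fear baseline is necessarily post-randomisation. What remains is that the Protocol does not name the screening score as baseline although a second W-DEQ is listed at registration, and that no CBSEI is described before allocation.

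**The order of registration is inferred, and so is knowledge of the group.** The sentence on registration looks back and does not say that registration follows randomisation. The Protocol does not say when women learn which arm each letter denotes. This is fair, and the point is therefore put as a possibility. Since participants are not listed as masked, the text does not exclude it.

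**The control-access sentence may not conflict with anything.** The app is said to have two main questionnaire stages, and the paragraph on the control group also names two later occasions. If registration takes place outside the app, the passages agree. If it takes place in the app, controls could not reach the baseline. The text does not settle which, so this calls for clarification and is not a proven contradiction.

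**Power is hardly affected on the Protocol's own inputs.** Correct, as column (a) shows. The fall to 71–74% at 10% wrong entries appears only with the back-solved 0.882 SD and is an illustration.

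**Conclusion.** The point holds in limited form and should be corrected. The Protocol fixes a procedure in which access to the intervention depends on an unverified entry by the participant. It also narrates an order in which the CBSEI baseline, and a second W-DEQ, may be answered with the group known.

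Random allocation itself is intact. The effect analysed as randomised shrinks by 2q for a wrong-entry share q in each arm, that is by 10% to 40% for assumed shares of 5% to 20%. This assumes equal shares in both arms and that a wrong letter persists for the whole intervention. Loss of power is negligible on the stated 21 and 7.2, and material only if the true standardised effect is far smaller. The baseline bias has no size that can be derived from the documents, but it would pass point for point into both change outcomes if the registration scores were used.

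**What to change.** - Replace the A/B selection with activation by the colleague who randomises, using a one-time code that carries the allocated group and cannot be changed by the participant.
- State that groups are analysed by the allocation list, whatever the app records show.
- Name the screening W-DEQ version A as the baseline for change in fear of childbirth. Because entry requires 38 or more on that score, some regression to the mean is likely, but it is the same in expectation in both arms.
- Collect CBSEI and demographics on that same occasion, before the allocation is opened, and drop the repeat W-DEQ at registration or give its purpose.
- Say whether the baseline is completed in the app, and align the sentence on control-group access with it.

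The cost is a small change to the app's configuration and a slightly longer screening step. No extra visit or staff is needed. If the trial has already run, the list can be compared with the letters recorded in the app, mismatches reported, and the time of the registration questionnaires relative to allocation stated.
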